| Design/Methodology:             | 
Migrants will be randomized to receive the intervention (<math>n = 60</math>) or wait list control (<math>n = 30</math>). Mental health outcomes (PHQ9, GAD7, PCL5) will be assessed at baseline during screening, throughout the intervention, post treatment, and at 1-, 3-, and 6- months follow-up. Demographic information, the IPL will be assessed at the time of enrollment. LEC5 will be assessed at baseline and at 1-, 3- and 6-month follow-up. Acceptability will be assessed after each session. All assessments will be conducted by the research team through a secure link in REDCap. Each migrant will participate in 5 assessment sessions and 6-12 intervention sessions with prior assessment of mental health outcomes. The intervention sessions have a frequency of once a week. In the case of the waitlist control, mental health outcomes will be assessed at baseline at the time of enrollment and at endline 12 weeks after baseline. Once the endline has been assessed, they will receive the intervention, with corresponding assessments as described previously. In the case of the providers, feasibility and acceptability will be assessed after each session. See Appendix for a graph of the design, schedule and assessments.
 |

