| Subject Participation Duration: | 
Enrollment and initial assessment: 1 online assessment of 30 min
 
Intervention: 6 to 12 online sessions of 60 min in 6 to 12 consecutive weeks. A link to assessments will be sent before each session.
 
Post treatment assessment: 1 online assessment of 30 min to be completed within 14 days after completion of the intervention.
 
1-, 3-, and 6-month follow-up assessment: 3 online assessments of 30 min scheduled at 1-, 3-, and 6-months after completion of the intervention.
                                                                                                                                                                                                                                                                                                                                                                                                                                                                                                                                                                                                                                                                                                                                 |

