## 4.2 Study Outcome Measures

### 4.2.1 Primary Outcome Measures

Since the intervention is transdiagnostic and addresses several CMD, there will be three primary outcome measures. Changes in anxiety will be measured using the GAD7 scale. This is a 7-item instrument that measures generalized anxiety. Changes in depression will be assessed using the PHQ9 questionnaire, which is a 9-item instrument that measures depression. Both instruments have been chosen because they are short, easy to administer and have been widely used in research. Spanish versions of GAD7 and PHQ9 have been validated and used in Venezuelan and Peruvian populations. Furthermore, prior studies with this same population conducted by the main researcher have used these instruments. Regarding PTSD, changes will be measured using the PCL5 checklist which has been validated for its use in Spanish-speaking populations and utilized in research projects with similar populations. The LEC5, which identifies potentially traumatic events in the life course of the participants, will be used at baseline and in the follow-up assessments along with the PCL5.

The primary outcomes will be measured at baseline during screening and at endline 12 weeks after baseline in the case of waitlist control. In the intervention group, they will be assessed at baseline during screening, weekly (PCL5) or every two weeks (PHQ9 and GAD7) throughout the intervention before the next session, after the last session of the intervention and at 1-, 3-, and 6-month follow-ups after completion of the intervention. Participants will be sent a secure REDCap link, where they will be asked to answer each item of the instruments.

See appendix with the English and Spanish versions of the instruments.

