There will be a planned variation in the dosage of the intervention, which can comprise 6 to 12 sessions. The exact number of sessions will be implemented according to the presentation of symptoms and difficulties of the participant. For instance, if the participant presents depressive symptoms concurrent with PTSD, then, strategies for the treatment of depression will be included alongside with strategies for the treatment of PTSD and the number of sessions will be higher. Also, some components identified as important for this population, such as problem solving or emotional regulation, could be added to the intervention, if they are identified as relevant for the specific participant. For instance, if - alongside with the CMD symptoms - the participant presents concrete problems that need to be tackled (e.g. precarious housing conditions, or lack of and need of childcare support), then the “problem-solving” component will be included as part of the intervention and the number of sessions will be higher. As described in detail in Section 8 “Study Intervention”, the first 6 sessions will be intended to treat the most urgent symptoms, and the following sessions will tackle other aspects relevant to the mental health of the participants.

As to the collection of data for the assessment of study objectives, the participant outcomes will be measured using validated instruments such as the PHQ9, GAD7, LEC5 and PCL5. In the case of the intervention group, all outcomes will be measured in the screening, after the last session and at 1-, 3- and 6-month follow-up. In the case of waitlist control, primary outcomes will be assessed at baseline during screening and at endline 12 weeks after baseline. For both the waitlist control and the intervention group, The PHQ9, GAD7, and PCL5 will be assessed throughout the intervention (which occurs at randomization for the intervention group, and 12 weeks after for the waitlist control group).

Furthermore, the assessment of secondary outcomes, such as acceptability and feasibility, will be measured as presented above, in section 4.

See the Appendix for a schematic of the study design.

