|-------------------------------------|--------------------------------------------------------------------------------------------------------------------------------------------------------------------------------------------|-------------------------------------------------------------------------------------------------------------------------------------------------------------------------------------------------------------------|
|                                     | May-August 2025

Third group of 30 participants:
August -November 2025                                                                                                            |                                                                                                                                                                                                                   |
| Sessions 7 to 12                    | First group of 30 participants:
May - August 2025

Second group of 30 participants:
August-November 2025

Third group of 30 participants:
November 2025-February 2026 | Individually with provider
Remotely via Meet or WhatsApp videocall
60 min duration
Focus on other aspects relevant to mental health (emotional regulation, problem solving, adaptation related distress) |
| Assessments throughout intervention | January 2025 to February 2026                                                                                                                                                              | Remotely via REDCap secure link (PCL5 every week before the session, PHQ9 and GAD7 every 2 weeks before the session, acceptability and adherence every week after each session)                                   |
| Endline                             | May 2025 to February 2026                                                                                                                                                                  | Remotely via REDCap secure link (PHQ9, GAD7, LEC5 and PCL5)
12 weeks after first session in intervention group (or within 14 days of completion).
12 weeks after baseline in waitlist control group.        |

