| Assessment at 1-month follow-up     | August 2025 to January 2026                                                                                                                                                                | Remotely via REDCap secure link (PHQ9, GAD7, LEC5, PCL5) one month after endline (or a maximum of a month later).                                                                                                 |
| Assessment at 3-month follow-up     | October 2025 to March 2026                                                                                                                                                                 | Remotely via REDCap secure link (PHQ9, GAD7, LEC5, PCL5) three months after endline (or a maximum of a month later).                                                                                              |
| Assessment at 6-month follow-up     | January to June 2026                                                                                                                                                                       | Remotely via REDCap secure link (PHQ9, GAD7, LEC5, PCL5) 6 months after endline (or a maximum of a month later).                                                                                                  |
| Data Analysis                       | June 2026 to July 2027                                                                                                                                                                     | Data analysis will take place using data analytic software and be used for publication and dissemination in scholarly journals and conferences.                                                                   |

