### 15.2 Sample Size Determination

The sample comprises  $n = 90$  pilot participants, of which  $n = 60$  will be randomly assigned to the intervention group and  $n = 30$  to a waitlist control. The sample size for pilot participants is based on a method outlined by Viechtbauer. Viechtbauer suggests that for a pilot trial a sample size of  $n = 59$  is sufficient to detect a problem that emerges for 5% of participants.

We expect participant recruitment to be feasible as the PI and colleagues at Universidad del Pacifico have recruited and engaged with over 2,000 research participants in mental health research. For example, for the prior stages of this project we have engaged  $n = 19$  experts and  $n = 29$  migrants.

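### Protocol Sections 2, 4.2.1/5 and 12 set different assessment schedules for the up to 30 waitlist participants after they cross over to treatment

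*Protocol*

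**What the plan says.** The sample is 90 participants, "of which $n = 60$ will be randomly assigned to the intervention group and $n = 30$ to a waitlist control". Section 5 states that all of them will be treated. Three sets of text then govern what is measured in waitlist participants after they cross over.

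- **Section 2 (Design/Methodology and Subject Participation Duration).** After the waitlist endline: "Once the endline has been assessed, they will receive the intervention, with corresponding assessments as described previously". The schedule set out just before that covers scores during treatment, a post-treatment assessment and three follow-ups. The follow-ups are "3 online assessments of 30 min scheduled at 1-, 3-, and 6-months after completion of the intervention". The same section also says "Each migrant will participate in 5 assessment sessions and 6-12 intervention sessions".
- **Sections 4.2.1 and 5.** Section 4.2.1: "The primary outcomes will be measured at baseline during screening and at endline 12 weeks after baseline in the case of waitlist control". Section 5 repeats this: "In the case of waitlist control, primary outcomes will be assessed at baseline during screening and at endline 12 weeks after baseline". Section 5 then adds PHQ9, GAD7 and PCL5 scores during the intervention for both arms. Both sections name the assessment after the last session and the 1-, 3- and 6-month visits for the intervention group only.
- **Section 12.** The endline row places the assessment "12 weeks after baseline in waitlist control group". In the intervention group it is 12 weeks after the first session, or within 14 days of completing treatment. The 1-month follow-up is "one month after endline (or a maximum of a month later"; the 3- and 6-month rows use the same anchor and the same window. No separate post-treatment visit is listed for the waitlist.

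**The concern.** In Section 12 the word endline has two meanings. For the intervention group it marks the end of treatment. For the waitlist it marks the end of the waiting period, before any session has been held. All three follow-up visits are counted from it, so the same visit label refers to different points in the course in the two arms. Sections 4.2.1 and 5 do not name those visits for the waitlist at all, while Section 2 does.

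Section 5 says all randomised participants enter the analyses. Section 15.3 plots trends over baseline, post-intervention and six months later. Section 4.2.2 defines retention by completion of all study visits and the follow-up assessment. For a third of the sample the sections disagree on whether the last two analysis points exist and what they are counted from, so retention has no single meaning for them. Visit timing has to be right in the protocol, because a visit missed or held at the wrong time cannot be recovered at the analysis stage.

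**Working it through.** **Inputs.** 60 intervention and 30 waitlist participants (Section 15.2); 6 to 12 weekly sessions (Section 8); the visit rules quoted above (Sections 2, 4.2.1, 5 and 12).

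**Step 1: reproduce the stated 5 assessments.** Subject Participation Duration lists 1 at enrolment, 1 post-treatment and 3 follow-ups: 1 + 1 + 3 = 5. This matches the stated figure for the intervention arm. It leaves out the waitlist's week-12 endline.

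**Step 2: count the waitlist visits by section (pre-session scores excluded).**

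| Source | Baseline | Week 12 | Post-treatment | 1, 3, 6 months | Total |
|---|---|---|---|---|---|
| Section 2 | 1 | 1 | 1 | 3 | 6 (stated: 5) |
| Sections 4.2.1 and 5 | 1 | 1 | none named | none named | 2 |
| Section 12, read literally | 1 | 1 | none | 3 | 5 |

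**Step 3: waitlist timeline under Section 12, in weeks after endline.** Assumptions: treatment starts at endline (lag 0) and session k takes place k − 1 weeks after the start. One month is 365.25 / 12 / 7 = 4.35 weeks, three months 13.04 and six months 26.09.

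- Last session: week 5 (6 sessions), week 7 (8 sessions), week 11 (12 sessions).
- Nominal 1-month visit, week 4.35, by which time 5 sessions have been held. 4.35 − 5 = −0.65 and 4.35 − 11 = −6.65, so it precedes the last session at every permitted course length. Start lags of 1, 2 and 4 weeks give the same result.
- End of the one-month window, week 8.70. With no lag, 6- and 8-session courses have finished (weeks 5 and 7) and a 12-session course has not (week 11). With a 4-week lag even a 6-session course has not finished (last session at week 9).
- Nominal 3-month visit, week 13.04. 13.04 − 11 = 2.0 and 13.04 − 5 = 8.0 weeks after the last session. With a 4-week lag and 12 sessions it falls 2.0 weeks before the last session (week 15).
- Nominal 6-month visit, week 26.09. 26.09 − 11 = 15.1 and 26.09 − 5 = 21.1 weeks after the last session.

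Counted from completion, as in Section 2, the three visits would fall about 4.35, 13.04 and 26.09 weeks after the course.

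**Step 4: number affected.** At most 30 / 90 = 33%.

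**The case against.** The strongest reply is that Section 2 already covers the crossover: it gives waitlist participants the same assessments as the intervention arm and counts follow-up from completion. On that rule every treated participant has a post-treatment score and no follow-up falls during treatment. The two-point sentences in Sections 4.2.1 and 5 can be read as describing the waiting period only. Section 5 supports this, since it adds during-treatment scores for both arms straight afterwards and so was not meant as a complete list. The appendix, to which the protocol refers for the design and schedule of events, is not shown and may record the intended schedule.

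Much of this stands, and it rules out several stronger readings.

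- A reader might infer that 30 treated participants will certainly lack post-treatment data. The documents do not support that: the outcome depends on which section staff follow.
- A reader might combine the missing post-treatment visit and the mid-treatment 1-month visit under every reading. Only literal Section 12 gives both. If Sections 4.2.1 and 5 are read as complete, there is no waitlist 1-month visit to be mistimed. Under Section 12 the 3-month visit usually follows the last session, so what is absent is a dedicated end-of-treatment visit, not every later score.
- A reader might take the stated 5 as evidence that a waitlist schedule without a post-treatment visit was intended. The itemised list in Section 2 includes one, so the match with the Section 12 count is a coincidence.
- A reader might want to put a figure on lost precision. Section 15.3 names no pooled within-treated estimate on all 90, so no such figure can be tied to the plan.

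The objection does not remove the Section 12 anchor. That is a stated rule, not a silence, and it conflicts with Section 2. Nor do during-treatment scores replace the missing visit: they are taken before sessions, with PHQ9 and GAD7 only every two weeks, so none follows the last session.

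**Conclusion.** The inconsistency is real and should be corrected. For up to 30 of 90 participants (33%) the protocol gives three schedules after crossover, with 6, 2 or 5 assessments depending on the section. Followed literally, Section 12 provides no end-of-treatment visit for them and puts the nominal 1-month visit 0.65 to 6.65 weeks before the last session when treatment starts at endline. The window softens this for some shorter courses. Their follow-up scores would then not be comparable with those of the intervention arm at the same label.

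The timing figures assume weekly sessions without rescheduling and a start at endline; later starts move the visits earlier relative to treatment. The randomised 12-week comparison uses no data from after the crossover and is not affected. What is exposed is any use of waitlist participants at the post-intervention and 6-month points, and the retention measure.

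**What to change.** Bring Sections 4.2.1, 5 and 12 into line with Section 2:

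- Label the waitlist's week-12 assessment as a pre-treatment endline.
- Schedule a separate post-treatment assessment for waitlist participants after their own course.
- Time the 1-, 3- and 6-month visits in both arms from completion of the participant's own intervention, and remove endline as the anchor in Section 12.
- Restate the number of assessment sessions as 5 for the intervention arm and 6 for the waitlist. The consent form, which is not shown, needs the same change only if it repeats the 5.
- Check the appendix schedule against the revised text.

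The cost is wording plus one 30-minute online assessment for up to 30 people, which Section 2 already implies. The last waitlist follow-ups will come later in the calendar, so the Section 12 dates must be updated. They need attention in any case: the third treatment group's sessions run to February 2026, while the 1-month follow-up row ends in January 2026 and the 6-month row in June 2026, only four months after February.

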## 6 Potential Risks and Benefits

### 6.1 Risks

It is unlikely that participants will be at risk of physical harm as a result of the study participation. The primary risks to participants are breach of confidentiality, fatigue or personal discomfort during the intervention sessions or assessments. Participants may find some of the topics addressed during the sessions or some of the questions asked during assessments to be emotionally upsetting and may experience short-term elevations in negative affect during active intervention sessions. As with any study of participants with mental illness, there is always the risk of symptom worsening. The weekly assessment of symptoms throughout the intervention will allow us to closely monitor any changes in the migrant participants and put in action a safety plan, in case of increased severity or suicidality. Weekly meetings with supervisors, who will be closely accompanied by the research team in weekly group meetings, will enable us to timely identify participants whose symptoms are not progressing as expected and to take timely action. At any point in the study if participants exhibit increasing severity of psychiatric symptoms that warrants a higher level of care, they will be referred to the local hospital. If symptoms require immediate medical management, participants’ family members will be contacted and recommended to bring the participant to the hospital emergency room.

Adaptation and assessment of a common element treatment protocol designed to improve mental health in forcibly displaced populations

Version 1, September 17, 2024

Furthermore, participants will be advised to call the hotline 113 to get in touch with counselors from the Peruvian mental health system or the number 106 in case they need an ambulance.

In the case of the provider participants, they may find some of the topics addressed during the sessions to be emotionally upsetting or may experience concern regarding the wellbeing of some participants. As mentioned above, frequent meetings with supervisors, closely accompanied by the research team, will enable us to discuss these concerns, to identify if the symptoms of a participant are not progressing as expected and to take timely action. Also, supervisions will provide with the opportunity to tackle the discomfort that a provider might be experiencing and to find means to alleviate it.

Other measure to be taken to protect the participants against risk are the following:

- Team of experienced investigators, with extensive background in forcible displacement and mental health
- Rigorous training on ethical conduct of human research for all personnel and project-related training on migration related trauma and understanding mental health. Also, specific training on processes aimed at guaranteeing privacy and confidentiality will be included.
- Measures to ensure privacy and confidentiality, such as making sure of the non-participation of others in the sessions, maintaining documents and information in locked secure settings, identifying individual subjects by study number without personal identifiers.
- Offering breaks to alleviate fatigue and distress; reminders of voluntariness of their participation in the study
- Plan for referral in case of risk of harm, severe depression and suicidality
- Re-experiencing trauma is a common concern, but the process of exposure has been demonstrated to be effective in hundreds of clinical trials for PTSD. The training and supervision of the providers will ensure the rationale, structure and skills to help participants appropriately engage with trauma stimuli.

